### Sample size calculation and statistics

A total of 1000 right-handed aMCI patients will be recruited in this study. aMCI-ε4 patients is about 26.6 %, and annual conversion rate of aMCI-ε4 patients convert is 15.9 % [22]. Thus, we plan to recruit 200 patients with aMCI-ε4. There will be about 90 aMCI-ε4 converted into AD after 3 years of follow-up.

Demographics and clinical characteristics of the subjects will be analyzed using SPSS 17.0. Two-sample two-tail *t* test or two-tail Pearson chi-square test will be used to explore differences of these data among two groups (converters and nonconverters). *P* < 0.05 is considered as with statistical significance.

For images analysis. To determine the difference between two groups (converters and nonconverters), we will perform a two-sample *t*-test. The significant level will be set at *P* < 0.05.

To determine the difference between intra-groups, we will perform a One-way analysis of variance (ANOVA). Further, Dunnett-*t* test will be performed for differences among intra-groups. The statistical threshold of the two test will both be set at *P* <0.05.

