**Discussion:**

This study is to find out the neuroimaging biomarker and the changing laws of the marker during the progress of aMCI-ε4 to AD, and the final purpose is to provide scientific evidence for new prevention, diagnosis and treatment of AD.

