Although the cognition evaluation is simple, the accuracy of the diagnosis depends on the professional skills of the doctor and the collaboration of patients. On the other hand, MRI might be a promising strategy for early diagnosis of AD [3]. MRI might be the best diagnosis method for AD by mapping both structures and functions of the human brain. Structurally, studies showed that brain atrophy in AD patients first appears in the medial temporal lobe (MTL), and then involves the parietal lobe, frontal lobe and occipital lobe, and finally the anterior cingulate cortex [4, 5]. Consistent with these findings, evidence from our team has demonstrated the progressive alterations of brain structures during the progression to AD [6]. Compared with APOE-ε4 non-carriers, the carriers exhibited greater medial temporal lobe atrophy [7]. APOE-ε4 is an independent risk factor for the hypotrophy hippocampus in patients with AD and MCI [8]. Decreased gray matter volume mainly restricts in the right brain area for aMCI-ε4 patients [9]. Not the degree of atrophy, but the rate of atrophy in a certain region of brain demonstrate close relationship with the AD progression [10]. The rate of hippocampal atrophy is suggested to be an early marker of incipient memory decline and dementia [11]. The longitudinal study indicated that rate of volumetric loss was significantly greater among MCI-ε4 compared with non-carriers [12]. Compared with structural MRI, diffusion tensor imaging (DTI) is a more sensitive method for detecting white matter damage [13]. A short-term follow-up study showed that AD patients had lower fractional anisotropy (FA) than controls in the fornix and anterior portion of the cingulum bundle, and these FA values were positively correlated with cognitive score [14]. The APOE-ɛ4 modulates white matter (WM) before clinical manifestations and cognitive impairment [15]. The changes of white matter is accompanied with the cognitive function decline in APOE-ε4 carriers [16]. Previous studies suggested that rs-fMRI is a potential functional biomarker for cognitive impairment. The aMCI subjects showed that posterior cingulate cortex/precuneus (PCC/PCu) hyper-functional connectivity was found at baseline, while a substantial decrease of these connections was observed at follow-up [17]. Our team observed that the aMCI patients had decreased amplitude of low-frequency fluctuations (ALFF) values in the PCC/PCu, anterior medial prefrontal cortex (aMPFC), hippocampus/parahippocampal gyrus (PHG), basal ganglia, and prefrontal regions, and increased ALFF values mainly in several occipital and temporal regions [18]. APOE-ε4 exerts an influence on brain function in patients with MCI. Using whole-brain pulsed arterial spin labeling (ASL) magnetic resonance imaging suggest that cognitive status and APOE genotype have interactive effects on cerebral blood flow (CBF) [19]. MCI-ε4 patients demonstrated significantly increased CBF [20]. However, deficits exist in these studies that using rs-fMRI to reveal the effect of APOE-ε4 on MCI patients.

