
For the purpose of early diagnosis, the researchers have been focusing on the aMCI window. Although previous studies provide important information for the conversion of aMCI to AD, they were based on the single modality neuroimaging analysis. Moreover, previous studies ignored one of the major factors that affects the course of the MCI converting to AD is the APOE-ε4. Thus, the purpose of the current trial is to longitudinally investigate the multi-modal (structural MRI, resting state-fMRI and diffusion tensor imaging) neuroimaging characteristics of aMCI-ε4 patients. We hope to provide scientific evidence for more effective prevention, diagnosis and treatment of AD.

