## Discussion

To our know, APOE-ε4 is a strong risk factor of AD. However, there has controversy about the effect of APOE-ε4 on the conversion of aMCI-ε4 to AD. A multivariate Cox regression model demonstrated that possession of an APOE-ε4 was the strongest predictor of clinical progression among aMCI [23]. Other studies of have found limited clinical applicability for prediction of outcome among aMCI [24, 25]. Moreover, Stern et al implied that APOE-ε4 is associated with a less aggressive form of AD [26]. Thus, previous studies have shown that simply depending on the psychometric tests will cause a noisy clinical data, and need biomarker to clarify the pathogenic mechanism of APOE-ε4, such as MRI, PET (positron emission tomography), and cerebrospinal fluid (CSF) examinations. Comparing to PET and CSF examinations, MRI ─ a noninvasive, nonradiation means ─ has been widely used with easy patient acceptance in both clinical and scientific studies.

Some limitations have to be took into account about this study. First, the trial's follow up time may be too short to be sured whether MCI-nonconverter would convert to AD in the future. Therefore, we will plan to continue to track the dynamic situations of these patients. Second, there has many technical problems of MRI. Data acquisition, data processing and data analysis of MRI are lack of standards. So far, no MRI model can be used for clinical diagnosis of AD. But we deeply believe that with the development of neuroimaging, diagnosis of AD with MRI will achieve better performance.

Here, this present study is to find out the neuroimaging biomarker and the changing laws of the marker during the progress of aMCI-ε4 to AD, and the final purpose is to provide scientific evidence for new prevention, diagnosis and treatment of AD.

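### The aim is longitudinal and scans are yearly, but no named analysis compares change over time between converters and nonconverters

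*Protocol article*

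**What the plan says.** **Aim.** The Background of the protocol article states that "the purpose of the current trial is to longitudinally investigate the multi-modal" imaging characteristics of aMCI-ε4 patients. The Discussion section of the Abstract and the main Discussion both say the study is to "find out the neuroimaging biomarker and the changing laws of the marker during the progress of aMCI-ε4 to AD". The Background also reports, from cited work, "Not the degree of atrophy, but the rate of atrophy in a certain region of brain demonstrate close relationship with the AD progression".

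**Data.** Under Follow up, every patient is examined and scanned at baseline and then yearly for about three years, so up to four scans each. Patients are then classed as converters or nonconverters by diagnosis during follow-up.

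**Image tests.** The section Sample size calculation and statistics names two:
- Between groups: "To determine the difference between two groups (converters and nonconverters), we will perform a two-sample" *t*-test, at *P* < 0.05.
- Within groups: "To determine the difference between intra-groups, we will perform a One-way analysis of variance (ANOVA"), followed by a Dunnett comparison, described as a "test will be performed for differences among intra-groups". Both are at *P* < 0.05.

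The article does not state which variable enters the *t*-test. It mentions no slope, change score, repeated-measures model or group-by-time term. The image-analysis sections define measures scan by scan (gray matter volume, cortical thickness, functional connectivity, FA, MD) and derive no change image or annual rate.

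**The concern.** If the aim is to learn how a marker changes as patients progress, and patients are split by whether they progress, one expects a test of whether the two groups change differently. No such test is named. Three problems follow if the listed tests are applied to the per-scan measures that the article defines:

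1. A *t*-test on follow-up levels cannot separate a gap already present at baseline from a different rate of change. It can be positive when the rates are equal, and weak when only the rates differ.
2. Testing change separately within each group does not compare the groups. Significant change in one and not in the other does not show that the rates differ.
3. A one-way ANOVA across visits ignores that the same patients are scanned each time. It leaves stable between-patient variation in the error term, which for strongly correlated measures costs most of the power to see change.

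At stake is whether the yearly scans answer the longitudinal question for which they are collected.

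**Working it through.** **What the article gives.** 200 patients, 15.9% annual conversion, about 90 converters expected at three years, yearly scans. It gives no effect size, SD or power, so there is no stated power figure to reproduce. Its one derived figure, about 90 converters, is not reproduced exactly: 200 × (1 − 0.841³) = 81.0 by compounding, and 200 × 3 × 0.159 = 95.4 by simple addition. This matters little here. The difference detectable with 80% power, (1.96 + 0.84) × √(1/n₁ + 1/n₂), is about 0.40 SD for 81/119, 90/110 and 95/105 alike.

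**Assumed for illustration.** 81 vs 119 patients; four complete visits at years 0 to 3; SD 1 at a visit; within-patient correlation 0.9, so residual variance 0.1; two-sided 5%. Between-patient slope SD *s* is 0 or 0.2 per year, independent of the baseline level. Slope difference is 0.1 SD/year.

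Common factor: √(1/81 + 1/119) = 0.1440. Power ≈ Φ(difference/SE − 1.96).

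| Variable entered in the two-sample test | SD, *s* = 0 | Power | SD, *s* = 0.2 | Power |
|---|---|---|---|---|
| Year-3 level (difference 0.3) | 1 | Φ(2.083 − 1.96) = 55% | √(1 + 9 × 0.04) = 1.166 | Φ(1.786 − 1.96) = 43% |
| Per-patient slope (difference 0.1) | √(0.1/5) = 0.141 | Φ(4.909 − 1.96) = 99.8% | √(0.02 + 0.04) = 0.245 | Φ(2.834 − 1.96) = 81% |
| Year 3 minus baseline (difference 0.3) | √0.2 = 0.447 | Φ(4.657 − 1.96) = 99.7% | √(0.2 + 0.36) = 0.748 | Φ(2.783 − 1.96) = 79% |

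The 5 in the slope variance is the sum of squared deviations of the visit times 0, 1, 2, 3 from their mean.

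With a slope difference of 0.05 SD/year, the year-3 level test has about 18% and the slope test 69% (*s* = 0), or about 14% and 29% (*s* = 0.2).

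**Equal slopes, baseline gap 0.4 SD** (*s* = 0). Year-3 level test: 0.4/0.1440 = 2.777, and Φ(2.777 − 1.96) = 79%; simulation gives about 78%. Slope test: about 5%, its nominal level.

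**One-way ANOVA across visits** (simulation, correlation 0.9, *s* = 0). These are rejection rates within a single group, against a one-sample test on per-patient slopes:

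| True change per year | n = 81: ANOVA / slope | n = 119: ANOVA / slope |
|---|---|---|
| 0.05 SD | 0% / about 89% | 0% / about 97% |
| 0.1 SD | 2% / 100% | 19% / 100% |

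Here the error is one of lost power, not of excess false positives.

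**The case against.** **The test may not be cross-sectional.** A reader might infer that the plan fixes a comparison of levels. The text does not say so. A two-sample *t*-test on change or slope images fits the same sentence, and under the assumed model change from baseline performs almost as well as the slope test (99.7% against 99.8%). This stands: the loss shown for the level test arises only if levels are entered. No change measure is defined anywhere, however, so levels are the plain reading.

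**A difference in rate is not the stated target.** A reader might also infer that it is, and that it goes untested. The article does not support that. The sentence on rate of atrophy is background from cited work. The aims speak of a biomarker, which a baseline contrast can serve, and of how the marker changes during progression, which could mean the course within converters. The ANOVA appears directed at the latter, so change is not wholly untested.

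**Condensed article.** The variable entered in a test is detail that an article may leave to the full protocol or analysis plan. Its absence alone would not be a finding. But the article does list its tests, the list contains no between-group comparison of change, and it commits to a one-way ANOVA. A fuller plan that followed this list would inherit both problems.

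**Illustration.** Power near 100% requires every patient in a group to share one true slope. At slope SD 0.3/year the slope test falls to 55%, against 34% for the year-3 level test. The ordering holds, but the gap narrows. A baseline gap between future converters and nonconverters would also be a legitimate biomarker result, provided it is labelled as one. Nothing in the article says the investigators will read separate within-group results as a difference in rates.

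**Conclusion.** The concern holds in this limited form. The purpose is longitudinal and scans are yearly, but the statistics section names no between-group test of change over time and leaves the *t*-test's input open. The ANOVA it names for intra-group differences is unsuitable if, as seems likely, it is to be run across visits.

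The size depends on what is entered and on variances that the article does not give. If levels are entered, the year-3 test has roughly 43% to 55% power where a slope test has 81% to 99.8% (slope difference 0.1 SD/year, slope SD 0.2 to 0). It would also reject about 78% of the time for a 0.4 SD baseline gap with identical slopes. If change scores were always intended, most of this loss disappears and the remedy is a clarifying sentence. In either case the matter should be settled before the images are analysed.

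**What to change.** - State what enters the converter/nonconverter *t*-test.
- For the longitudinal question, test group by time in a linear mixed model with random intercept and slope per patient and actual scan date as time. For voxel maps, apply the two-sample *t*-test to per-patient slope or change images. Report the difference in annual change with its 95% confidence interval.
- Replace the one-way ANOVA for within-group change with a repeated-measures model.
- Report the baseline converter/nonconverter contrast as a separate, labelled biomarker question.

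The cost is revised analysis wording and slightly more analysis work. The yearly scans are already planned, so no new data are needed.

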**Methods/Design:**

In this study, 200 right-handed subjects who are diagnosed as aMCI with APOE-ε4 will be recruited at the memory clinic of the Neurology Department, XuanWu Hospital, Capital Medical University, Beijing, China. All subjects will undergo the neuroimaging and neuropsychological evaluation at a 1 year-interval for 3 years. The primary outcome measures are 1) Microstructural alterations revealed with multimodal MRI scans including structure MRI (sMRI), resting state functional MRI (rs-fMRI), diffusion tensor imaging (DTI); 2) neuropsychological evaluation, including the World Health Organization-University of California-LosAngeles Auditory Verbal Learning Test (WHO-UCLA AVLT), Addenbrook’s cognitive examination-revised (ACE-R), mini-mental state examination (MMSE), Montreal Cognitive Assessment (MoCA), Clinical Dementia Rating scale (CDR).

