#### MRI image analysis

sMRI data analysis. Voxel-based morphometry (VBM) with DARTEL will be used to characterize gray matter volume (GMV). Voxel-based morphometry with DARTEL will be performed using SPM8 (Welcome Trust Center for Neuroimaging, London, UK, http://www.filion.ucl.ac.uk/spm/software/spm8/). For the analysis of cortical thickness, we will use the software package of the Montreal Neurological Institute (MNI)(http://wiki.bic.mni.mcgill.ca/index.php/CIVET). This process includes structural image non-uniformity correction, spatial standardization, tissue segmentation (gray matter, white matter and cerebrospinal fluid), internal and external surface extraction of gray matter as well as the definition and measurement of cortical thickness.

rs-fMRI data analysis. Image preprocessing will be performed by using SPM8 (http://www.fil.ion.ucl.ac.uk/spm/) and Data Processing Assistant for Resting-State fMRI. The preprocessing procedures will be performed including removal of the first 10 volumes, slice timing, and head motion correction. All rs-fMRI data will be satisfied the criteria of spatial movement in any direction < 3 mm or 3^o^ and the subjects will be demonstrated no significant group differences in the head motion parameters (i.e, three translation and three rotation parameters). To normalize the fMRI data spatially, the T1-weighted images will be firstly registered to the mean functional data, and the resulting aligned T1 data set will be segmented and transformed into MNI space using the DARTEL toolbox, and a group template will be generated. Next, the motion-corrected functional volumes will be specially normalized to the group template using the transfer parameter estimated by DARTEL segmentation and resampled to 3 mm isotropic voxels. Further, the functional images will be spatially smoothed with a 4 mm Gaussian kernel. The linear detrend and temporal bandpass filtering (0.01 – 0.08 Hz) will be performed to reduce the influences of low-frequency drift and high-frequency physiological noise. Finally, several nuisance signals will be regressed out from the data, including the six motion parameters, the global, the white matter, and the cerebrospinal fluid signals.

Functional connectivity (FC) analysis using DPARSF software (http://www.restfmri.net/forum/DPARSF).

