DTI data analysis. DTI data processing will be carried out using FSL software (FMRIB Software Library, http://www.fmrib.ox.ac.uk/fsl). Initially, eddy current correction will be run to correct gradient-coil distortions and small-head motions using affine registration to a reference image (b0 volume). The brain voxels of DTI data will be extracted using the Brain Extraction Tool (BET). The maps of diffusion tensor parameters including FA and MD will be calculated using DTI-FIT tool, which fits a diffusion tensor model to diffusion-weighted images for each voxel. Voxel-wise statistical analysis of the FA and MD data will be performed for regional differences using TBSS.

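### The converter versus nonconverter image test is set at P < 0.05 with no correction named, although the grey matter, FA and MD analyses are voxel-wise

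*Protocol article*

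**What the plan says.** All references are to the Protocol article.

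- **Outcomes.** The Abstract (Methods/Design) places imaging among the primary outcomes: "The primary outcome measures are 1) Microstructural alterations revealed with multimodal MRI scans". It lists structural MRI, resting-state fMRI and DTI without ranking them.
- **Units of analysis.** MRI image analysis states, for structure, "Voxel-based morphometry (VBM) with DARTEL will be used to characterize gray matter volume (GMV"), and for diffusion, "Voxel-wise statistical analysis of the FA and MD data will be performed for regional differences using TBSS". It adds cortical thickness and functional connectivity, but gives only software and processing for them, not the unit at which groups are compared.
- **Test and level for images.** Sample size calculation and statistics states: "To determine the difference between two groups (converters and nonconverters), we will perform a two-sample *t*-test". The next sentence is "The significant level will be set at *P* < 0.05".
- **Intra-group tests.** The same section plans a one-way ANOVA, then: "Further, Dunnett-*t* test will be performed for differences among intra-groups". The level is given as: "The statistical threshold of the two test will both be set at *P* <0.05".

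No section names a family-wise, false-discovery, cluster, permutation or small-volume correction, and none names a primary map or region. The level for the images is the same 0.05 that the section sets for single demographic and clinical variables.

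**The concern.** A voxel-wise analysis runs one test per voxel. A level of 0.05 that is suitable for one comparison of, say, age is then applied tens of thousands of times per map. The study aims to identify a neuroimaging biomarker of conversion in ε4 carriers. If practically every voxel-wise map yields some significant region whether or not the groups differ, finding one is no evidence for a biomarker. This affects the primary imaging outcome. It comes from a threshold that the article sets, not from detail it leaves out.

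**Working it through.** **Inputs from the article.** Level 0.05; two-sample t-test (sidedness is not stated for images, so two-sided is assumed); 200 patients, about 90 converters, hence 200 − 90 = 110 nonconverters. Voxel-wise maps: grey matter volume, FA and MD. Unit not stated: cortical thickness and functional connectivity.

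**Assumption.** The number of voxels tested is not given. A brain volume of 1.2 to 1.9 L on 3 mm voxels (27 mm³ each) is assumed. The article states 3 mm resampling only for resting-state fMRI, so this is an illustration for the other maps.

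**Step 1. The plan's own figure.** The 0.05 is a chosen level, not a derived one. It is the error rate of one test: 1 − 0.95¹ = 0.05.

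**Step 2. Chance of at least one false positive in m independent tests, 1 − 0.95^m.**

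| m | chance |
|---|---|
| 50 | 92.3% |
| 59 | 95.2% |
| 100 | 99.4% |
| 200 | above 99.99% |

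**Step 3. Expected false-positive voxels per null map, 0.05 × voxels.** This does not require independence.

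- 1,200,000 / 27 ≈ 44,400 voxels; 0.05 × 44,400 ≈ 2,200
- 1,900,000 / 27 ≈ 70,400 voxels; 0.05 × 70,400 ≈ 3,500

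**Step 4. Does spatial correlation rescue the rule?** Neighbouring voxels are correlated, so Step 2 cannot be applied to the raw voxel count. Smooth Gaussian null maps were simulated as an approximation to t-maps: 57,920 voxels of 3 mm (1.56 L), threshold |z| > 1.96, 300 maps at each smoothness.

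| Smoothness (FWHM) | Maps with any false positive | Mean voxels passing | Mean clusters | Median largest cluster (voxels) |
|---|---|---|---|---|
| 4 mm | 100% | 2,896 | 1,848 | 13 |
| 8 mm | 100% | 2,899 | 343 | 101 |
| 12 mm | 100% | 2,890 | 116 | 249 |
| 20 mm | 100% | 2,923 | 31 | 620 |

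Smoothness reduces the number of false clusters and enlarges them. It did not leave a single map clean.

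**Step 5. Across maps.** With only one test per map, five independent maps would give 1 − 0.95⁵ = 22.6%. Correction within each map therefore leaves the question across maps open. An equal division is 0.05 / 5 = 0.01 per map.

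**Step 6. Cost of correction.** Detectable standardized difference at 80% power: d = (z for α/2 + 0.842) × √(1/90 + 1/110), where the root is 0.142.

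- α = 0.05: (1.960 + 0.842) × 0.142 ≈ 0.40
- Bonferroni over an assumed 50,000 voxels, α = 0.05 / 50,000 = 1e-6: (4.892 + 0.842) × 0.142 ≈ 0.82

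Bonferroni is the conservative bound; permutation methods that use the spatial correlation are less strict. The article's 15.9% annual conversion, compounded, gives 200 × (1 − 0.841³) = 81 converters rather than 90. With 81 versus 119 the two values are 0.40 and 0.83, so the conclusion does not depend on that figure.

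**The case against.** The strongest reply is that the article never writes *uncorrected* or *per voxel*. A level of 0.05 can be the level of a corrected test, and a condensed article may leave the correction method to a fuller document. In part this stands: a corrected level may have been meant, and the near-certain error rate holds only if the rule is applied per voxel as written. It does not remove the point. The article does fix the image threshold, nothing says it is corrected, and the two readings differ widely (detectable d of 0.40 against up to 0.82).

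Other limits also stand:

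- A reader might infer that all five image measures are tested voxel by voxel across the whole brain. Voxel-wise testing is explicit for FA and MD and follows from the method for grey matter volume. Cortical thickness and functional connectivity could be regional.
- A reader might infer that the plan contains no multiplicity procedure at all. Dunnett's test is one. It acts among the intra-group comparisons, not across voxels, maps or modalities, and not on the converter versus nonconverter t-test.
- A reader might pool the five image measures with the five neuropsychological instruments as ten tests and quote 1 − 0.95¹⁰ = 40%. The image rule does not cover those instruments. Independence is also doubtful: the cognitive scales overlap, and FA and MD come from one tensor fit.
- A reader might infer that the reported regions would be mostly noise. A null simulation shows how often something is declared when nothing differs. It does not give the share of false regions when real differences exist, and the Background cites evidence that such differences may exist.

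**Conclusion.** The point holds for the voxel-wise maps of grey matter volume, FA and MD. Followed as written, the rule gives an essentially 100% chance of at least one false-positive region per map, with about 2,200 to 3,500 voxels passing under the null for an assumed 44,000 to 70,000 voxels. The voxel count, the 3 mm grid and the two-sided test are assumptions, but the conclusion is insensitive to them: 59 effectively independent tests suffice for 95%, and every simulated null map failed at each smoothness from 4 to 20 mm. For cortical thickness and functional connectivity the point is conditional on vertex-wise or voxel-wise testing. The documents do not show that uncorrected testing was intended. They show a stated threshold that does not control error at the unit of analysis they prescribe.

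**What to change.** 1. In the image paragraph of Sample size calculation and statistics, replace the plain level with: *family-wise error corrected P < 0.05 within each map, by permutation (for example threshold-free cluster enhancement in FSL randomise)*. FSL is already used for the DTI data.
2. Apply the same correction to any ANOVA or Dunnett test that is run voxel-wise.
3. State the unit of testing for cortical thickness and functional connectivity. If it is the vertex or voxel, apply the same rule.
4. Label findings across the several maps as exploratory, unless one map or region is pre-named as primary or the level is divided across maps (for example 0.01 each for five).

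Pre-naming one region per modality as primary, with Holm's procedure across the three, is a possible further step. It would redefine the primary outcome and is optional.

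The change costs wording and computing time, with no new data or visits. Fewer regions will reach significance, and the detectable difference per voxel rises from d = 0.40 to at most about 0.82 (80% power, 90 versus 110, Bonferroni bound for an assumed 50,000 voxels). Dividing the level across maps as well would raise it further.
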